## Abstract

**Background:**

Burnout has received limited attention in treatment programs, despite high prevalence among health professionals and the threat burnout places upon the mental health and the long-term sustainability of the Australian healthcare system. As part of The Essential Network (TEN), a blended care mental health support service for Australian health professionals, we developed Navigating Burnout – a digital cognitive-behavioural therapy program for health professional burnout. This three-arm randomised-controlled trial (RCT) will examine the effectiveness, acceptability, and cost-effectiveness of Navigating Burnout in both blended care and digital formats in reducing burnout among doctors.

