### Trial design

2.1

We will conduct a three-arm RCT to compare the effectiveness, acceptability, and cost-effectiveness of Navigating Burnout in reducing burnout among doctors across three delivery modalities.

Medical doctors (n = 207) will be randomly allocated to receive either [1] a blended version of the program combining the digital Navigating Burnout resources with five fortnightly telehealth sessions with a clinical psychologist [2]; a digital-only, self-guided version of the Navigating Burnout program; or [3] an active attention control where participants will be provided with digital self-care psychoeducation via email each fortnight. Across all conditions the treatment phase across will last 10 weeks.

We will measure self-reported burnout, psychosocial wellbeing, workforce engagement, and workforce attrition intentions before treatment, immediately after treatment, and 3 months after completing treatment (see Fig. 1 for trial design). This design will enable us to examine the effectiveness and acceptability of blended care Navigating Burnout compared to self-guided Navigating Burnout, as well as to examine the effectiveness of self-guided Navigating Burnout relative to an appropriate control.

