### Participants

2.2

Individuals will be eligible to participate in the trial if they satisfy all of the following criteria.•registered doctor currently practising in Australia;•able to read and speak English fluently;•current experience of self-reported burnout;•able to access the internet in a private location on a device suitable for viewing websites and attending telehealth consultations; and•able to attend telehealth consultations during Monday to Friday business hours (9.00–17.00).

Individuals will be excluded from trial participation if they satisfy any one or more of the following criteria.•current diagnosis of severe mental illness that requires more specialist support (e.g., bipolar disorder, schizophrenia, etc.);•current engagement with person-to-person psychological therapy (e.g. cognitive-behavioural therapy);•DASS-21 symptom scores in the Severe or Extremely Severe ranges for anxiety or depression during screening; or•report suicidal ideation or problematic alcohol or drug use during screening.

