**Fig. 2 fig2:**
[figure not shown]
Example screenshot from Navigating Burnout.

In the blended care arm, a clinical psychologist from the BDI Clinical Service will work through the Navigating Burnout content with participants over 10 weeks in five fortnightly 1-hour consultations. Clinical psychologists will follow a treatment manual mirroring the content of Navigating Burnout, with guidance on integrating digital content into session activities. Session 1 covers understanding burnout and self-care, session 2 covers unrealistic expectations, session 3 covers setting limits, session 4 covers valued living, and session 5 covers increasing social connections and information for managers. Session 1 is fixed and the same for all participants, whereas sessions 2–5 occur in an order determined by the participant and their clinical psychologist. Clinical psychologists will be offered a training program comprising [1]: a comprehensive treatment manual summarising the study protocol, the digital content, and session plans with suggested approaches to delivering the program's CBT strategies [2]; a 90-min protocol training session delivered by PB covering the design and purpose of the study, how to use the training manual, how to embed the digital content in a standard telehealth consultation, and roleplays of case examples; and [3] optional monthly 60-min clinical supervision sessions with PB. Clinicians will have discretion to tailor consultations to participant needs as long as (a) the clinical focus remains burnout; and (b) the program content is delivered in full across the five consultations. Participants will also have independent access to the digital version of Navigating Burnout over the 10 weeks between consultations and be directed by their clinical psychologist to specific components of the program in order to support awareness and management of burnout. During the 10-week treatment period, clinical psychologists providing care in the blended arm will provide immediate risk assessment and intervention for any participant expressing intent to self-harm or suicide and report any concerns related to suicide or self-harm attempts to PB.

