To examine the cost-effectiveness of blended (therapist-guided) Navigating Burnout, direct costs of the blended care arm will be quantified (computed as actual service delivery costs incurred by BDI) alongside indirect costs such as lost productivity of recipients due to use of the intervention (computed as average role wage multiplied by time taken out of work where sessions are attended during work hours, then annualised and adjusted for average FTE). Due to a lack of standardised and established estimates of the economic cost of burnout using commonly used measures, the benefits of blended Navigating Burnout will be compared against the value of improvements in occupational outcomes (WHO-HPQ; TIS-6), computed as average role wage multiplied by additional work engagement over the period of measurement, then annualised and adjusted for average FTE. Comparisons of these costs and benefits between treatment arms will provide an estimate of the net benefit and cost-effectiveness of blended Navigating Burnout. One-way and multi-way sensitivity analyses will be performed on assumptions in the model, such as cost estimates of lost productivity due to treatment and the relationship between turnover intention and actual turnover.

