## Discussion

5

TEN is Australia's only blended care mental health support service designed by-and-for health professionals. While TEN has already shown strong promise in assisting health professionals to manage psychological distress, there is scope to improve and expand the service to better meet the needs of health professionals through programs designed to manage and reduce the symptoms of burnout among health professionals.

Through careful design to cater for the specific needs and demands placed on health professionals and considering their workplace culture, our Navigating Burnout digital program has the potential to address the dearth of effective treatment programs readily available to health professionals. This RCT will provide strong evidence that is expected to support not only the acceptability, but also the therapeutic efficacy and cost-effectiveness of Navigating Burnout in supporting doctors experiencing burnout across both self-guided and blended modalities. If found to be effective in this group, further evaluation in other health professional groups could also be considered.

If the results of this trial indicate high levels of acceptability and therapeutic benefit from blended care Navigating Burnout, the program will be incorporated into TEN's existing person-to-person blended care model to provide clinical psychologists treating health professionals with a guide to treating burnout using CBT and ACT. Alongside this, the digital Navigating Burnout program may act as an adjunct to therapy between person-to-person consultations.

With evidence of the cost-effectiveness of both blended care and self-guided Navigating Burnout, we expect the outcomes of this study to provide healthcare organisations across Australia with a valuable method to enhance the management of health professional well-being. Specifically, organisations would have the rationale and necessary clinical protocol to take a stepped approach to supporting doctors through burnout [1]: offering the digital Navigating Burnout tools as a self-guided format for people with mild or moderate symptoms of burnout or people reporting burnout who are waiting for person-to-person care from a mental health provider; and [2] partnering with their Employee Assistance Program or local mental health providers to offer the blended Navigating Burnout program.

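### The economic analysis defines costs and a net-benefit output only for the blended arm, though cost-effectiveness is claimed for both formats, and it annualises the time cost of a one-off course but not its direct cost

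*Protocol article*

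**What the plan says.** **Aims and conclusion.** The Abstract (Background) says the trial will examine the "cost-effectiveness of Navigating Burnout in both blended care and digital formats". The last paragraph of the Introduction repeats this aim for both modes of delivery, and Trial design (2.1) extends the comparison to three modalities. The Discussion opens its recommendation of a stepped approach for healthcare organisations with the words "With evidence of the cost-effectiveness of both blended care and self-guided Navigating Burnout".

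**Method.** The cost-effectiveness paragraph of Statistical methods (2.13) is framed around the blended version. It has three terms:

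- Direct cost: "direct costs of the blended care arm will be quantified (computed as actual service delivery costs incurred by BDI").
- Indirect cost, with lost productivity as the worked example: "average role wage multiplied by time taken out of work where sessions are attended during work hours, then annualised and adjusted for average FTE".
- Benefit, from the WHO-HPQ and TIS-6: "average role wage multiplied by additional work engagement over the period of measurement, then annualised and adjusted for average FTE".

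The paragraph then says these costs and benefits will be compared between arms, giving the net benefit and cost-effectiveness of the blended version. One-way and multi-way sensitivity analyses are planned. The examples given are the cost of productivity lost to treatment and the link from turnover intention to actual turnover.

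**Course and follow-up.** Interventions (2.3) describes the blended course as delivered "over 10 weeks in five fortnightly 1-hour consultations". Outcomes are measured "before treatment, immediately after treatment, and 3 months after completing treatment" (Trial design).

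**The concern.** There are two separate problems.

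**Scope.** The aims and the Discussion need a cost-effectiveness result for the self-guided program. The method defines no cost for the self-guided or control arm and names no self-guided output. The only worked indirect cost is session time, and only the blended arm has sessions. If the paragraph is followed as written, the statement about self-guided cost-effectiveness has no analysis behind it, yet it underlies advice to healthcare organisations.

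**Time basis.** The direct cost and the time cost arise from the same five sessions. One is taken as incurred and the other is annualised, although a participant completes the course once. Benefits are also annualised, which carries an effect last observed at 3 months post-treatment forward without saying that it is assumed to persist. No common horizon is stated. The sign of the net benefit may therefore depend on a scaling choice that readers cannot see.

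**Working it through.** The protocol article gives no economic figure, so there is none to reproduce.

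**Step 1. Scope, side by side.**

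| Element | Blended | Self-guided | Control |
|---|---|---|---|
| Cost-effectiveness aim (Abstract, Introduction) | yes | yes | – |
| Cost-effectiveness evidence relied on (Discussion) | yes | yes | – |
| Direct cost defined (2.13) | yes | no | no |
| Worked time cost (2.13: session time) | yes | no sessions | no sessions |
| Named output (2.13) | yes | no | no |

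**Step 2. What annualising does to the time cost.**

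- Session time: 5 × 1 h = 5 h per participant, once (Interventions). This is a maximum, since it counts only if every session falls in the participant's work hours. That is possible, because participants must be "able to attend telehealth consultations during Monday to Friday business hours" (Participants).
- Measurement window: 10 weeks plus 3 months. Taking 3 months as 13 weeks gives 23 weeks.
- Annualised hours = 5 × 52 / weeks.
 - From the 23-week window: 5 × 52/23 = 5 × 2.26 = 11.3 h.
 - From the 10-week treatment phase: 5 × 52/10 = 5 × 5.2 = 26 h.

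The document does not say which factor is meant, so these are illustrations of a literal reading.

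**Step 3. Effect on net benefit.** Let W be the hourly wage, b the benefit in work hours over 23 weeks, and D the direct cost per participant. All three are assumed, because the document gives none. W is set at 100, D runs from 500 to 2,500, and b runs from 5 to 30. The four bases are:

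- A, all terms over 23 weeks: 100b − 500 − D
- B, as written with a 23-week factor: 100b × 52/23 − 500 × 52/23 − D
- C, as written with a 10-week factor for time: 100b × 52/23 − 500 × 5.2 − D
- E, one-year horizon with one-off costs counted once: 100b × 52/23 − 500 − D

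With D = 1,000 and b = 10:

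- A = 1,000 − 500 − 1,000 = −500
- B = 2,261 − 1,130 − 1,000 = about +130
- C = 2,261 − 2,600 − 1,000 = −1,339
- E = 2,261 − 500 − 1,000 = +761

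Across the assumed range:

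| D | b | A | B | C | E |
|---|---|---|---|---|---|
| 500 | 30 | +2,000 | +5,152 | +3,683 | +5,783 |
| 1,000 | 10 | −500 | +130 | −1,339 | +761 |
| 1,500 | 15 | −500 | +761 | −709 | +1,391 |
| 2,500 | 20 | −1,000 | +891 | −578 | +1,522 |
| 2,500 | 5 | −2,500 | −2,500 | −3,970 | −1,870 |

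The sign agrees at the extremes and changes with the time basis in between.

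**Step 4. Direction.** Against a coherent one-year horizon (E), the literal rule lowers net benefit by 500 × (2.26 − 1) = 630 under B, or by 500 × (5.2 − 1) = 2,100 under C. Against a within-trial horizon (A), it can raise net benefit (B at b = 10: +130 against −500) or lower it (C at b = 10: −1,339 against −500).

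**The case against.** The strongest reply is that this is one paragraph in a journal article and that annualised is undefined. It may mean no more than conversion to a yearly, FTE-adjusted basis, and a fuller plan could set the horizon. This stands as far as size is concerned: the factors of 2.26 and 5.2 cannot be attributed to the authors. It does not remove the point, because the text attaches the operation to one cost of a single course and not to the other.

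A reader might infer that setting annual benefits against unscaled direct costs flatters the intervention by about 2.3 times. The documents do not support that. On a one-year horizon it is normal to count a one-off direct cost once, and the ratio then only reflects the difference between 12 months and 23 weeks. The term in question is the scaled time cost, and overstating that works against the blended arm.

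A reader might also infer that the net benefit is arbitrary, or that no incremental result can be formed. Both go too far. The result would still depend on trial data. The sensitivity list is open-ended and already includes the cost of lost productivity, although persistence and horizon are not named. The planned comparison between arms suggests that some comparator cost may be intended, and self-guided delivery consists of a link and reminders, so its cost may be small. But no such cost is defined, and the named output remains blended-only. That is a mismatch with the stated aim, beyond a missing detail.

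Finally, cost-effectiveness is not among the listed primary or secondary outcomes. That limits the severity.

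**Conclusion.** The point holds on two counts.

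The scope mismatch rests on the text alone: cost-effectiveness is an aim and an expected conclusion for both formats, while the method defines costs and an output for one.

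The time-basis fault holds on a literal reading. A time cost of at most 5 hours would be counted as about 11 to 26 hours, while the direct cost of the same sessions is counted once. Benefits are carried beyond 3 months post-treatment without a stated persistence assumption. The hours assume a 23-week or 10-week base and every session in work time. The net-benefit figures also rest on an assumed wage, direct cost and benefit, and show only that the sign can change. Neither the size nor the direction of any bias can be fixed from the document. The primary analysis of burnout is unaffected.

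**What to change.** In Statistical methods (2.13):

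1. State one time horizon for every term, and define annualised if the word is kept.
2. Count the one-off direct and time costs of the course once. Either a within-trial or a 12-month horizon is coherent on this basis.
3. Label any benefit beyond 3 months post-treatment as an extrapolation, and add its persistence to the sensitivity analyses already planned.
4. Apply the same costing to the self-guided and control arms, and report incremental net benefit for blended versus self-guided and for self-guided versus control. Otherwise, limit the cost-effectiveness aim and conclusion in the Abstract, Introduction and Discussion to the blended format, and align Trial design.

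The cost is revised wording plus modest costing work on existing records. The estimated net benefit may change, up or down. Randomisation, data collection and the primary outcome are not touched.

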## Ethics approval and trial registration

3

This RCT was approved by UNSW Human Research Ethics Committee (iRECS4616). All methods will be carried out in accordance with relevant guidelines and ethical approval granted by UNSW Human Research Ethics Committee. The RCT is registered with the Australian New Zealand Clinical Trials Registry (ACTRN12624000124538).

## Results

4

It is anticipated that this trial will see improvement in burnout symptoms from baseline to 3 months post-treatment in both intervention arms (blended care and self-guided), with a more significant effect in the blended care arm. It is also anticipated that the trial will lead to improvements in the secondary aims and outcomes (anxiety and depression, psychosocial functioning, workforce participation, and workforce attrition intention) from baseline to 3 months post-treatment.

The active attention control is expected to be clinically inert (i.e. have no measurable effects on burnout outcomes, or the psychosocial and workforce secondary outcomes). However, the use of self-care materials by participants in the control arm may lead to some incidental improvements.

Navigating Burnout is expected to evidence high service acceptability among participants, and to be capable of implementation in a cost-effective manner.

## Discussion

5

TEN is Australia's only blended care mental health support service designed by-and-for health professionals. While TEN has already shown strong promise in assisting health professionals to manage psychological distress, there is scope to improve and expand the service to better meet the needs of health professionals through programs designed to manage and reduce the symptoms of burnout among health professionals.

Through careful design to cater for the specific needs and demands placed on health professionals and considering their workplace culture, our Navigating Burnout digital program has the potential to address the dearth of effective treatment programs readily available to health professionals. This RCT will provide strong evidence that is expected to support not only the acceptability, but also the therapeutic efficacy and cost-effectiveness of Navigating Burnout in supporting doctors experiencing burnout across both self-guided and blended modalities. If found to be effective in this group, further evaluation in other health professional groups could also be considered.

If the results of this trial indicate high levels of acceptability and therapeutic benefit from blended care Navigating Burnout, the program will be incorporated into TEN's existing person-to-person blended care model to provide clinical psychologists treating health professionals with a guide to treating burnout using CBT and ACT. Alongside this, the digital Navigating Burnout program may act as an adjunct to therapy between person-to-person consultations.

With evidence of the cost-effectiveness of both blended care and self-guided Navigating Burnout, we expect the outcomes of this study to provide healthcare organisations across Australia with a valuable method to enhance the management of health professional well-being. Specifically, organisations would have the rationale and necessary clinical protocol to take a stepped approach to supporting doctors through burnout [1]: offering the digital Navigating Burnout tools as a self-guided format for people with mild or moderate symptoms of burnout or people reporting burnout who are waiting for person-to-person care from a mental health provider; and [2] partnering with their Employee Assistance Program or local mental health providers to offer the blended Navigating Burnout program.

## Limitations

6

The self-guided digital Navigating Burnout program is currently publicly available through TEN without need for registration or an account. This decision followed the broad rationale behind TEN's development to reduce barriers to help-seeking and minimise health professionals' concerns around confidentiality. As such, there is a risk of contamination in the active attention control arm whereby participants could potentially access Navigating Burnout outside of the scope of the trial. To minimise the risk of contamination, references to TEN and Navigating Burnout will be omitted from recruitment materials and the PISCF.

Due to the nature of the funding for the trial, the participant population is limited to registered doctors. While this may limit the generalisability of findings to other health professionals, health professionals often share similar occupational environments and vulnerability to burnout. As such, there is a strong rationale for the applicability of findings to other health professional groups. A final limitation is that this intervention addresses the individual factors of burnout but does not directly address the more substantial systemic causes which, while beyond the scope of our study, urgently require greater attention.

## Conclusion

7

In conclusion, there is a critical lack of established mental health services or treatment programs specifically for burnout in health professionals. The present trial has the potential to provide clear data on implementing digital cognitive-behavioural therapy for burnout into a blended care model, with such findings being essential to ensuring an effective, well-functioning, and sustainable health system for the benefit of the broader Australian community.

## Data availability statement

As a clinical trial protocol, no data is presented as part of this publication.

